### Sample size

2.5

This is a non-inferiority verification study with QoL and efficacy as the main index. In the pilot study, incomplete CRM rate was 6.1% (2 out of 33 patients) in the L-ELAPE group. Based on the previous studies, we assume that the rate of incomplete CRM in the L-ISR group was 8.1% which was the average value in the meta-analysis.^[30]^ The adjusted formula below is used to calculate the sample size^[31]^ (Fig. 2). The “Pe” and “Pc” are the rates of incomplete CRM of the experiment group and the control group, respectively. The “k” represents the ratio of 2 groups’ sample sizes which equals 1 in this trial and “p” represents the joint probability. Setting type I error probability **α** = 0.025, type II error probability **β** = 0.2, the sample size required for each group is 72 cases. Furthermore, we assume that there will be a 20% dropout rate. Therefore, at least 159 patients are needed in this specific trial.

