### Outcome measures

2.4

The primary outcomes of this trial are to be scores of European Organization for Research and Treatment of Cancer QoL questionnaire-core 30 (QLQ-C30), QoL questionnaire-colorectum 29 (QLQ-CR29), Wexner Incontinence Score, International Prostate Symptom Score (for male), International Index of Erectile Function-5 (for male) and Female Sexual Function Index (for female). General QoL is assessed basically by scores of European Organization for Research and Treatment of Cancer QLQ-C30 version 3.0^[24]^ and QLQ-CR29.^[25]^ Defecation functions (daily defecation, frequency, urgency, incontinence, differentiation between defecation and gas emission, pad use, antidiarrheal drug use, and the presence or absence of erosion around the anus) are evaluated by the Wexner Incontinence Score.^[26]^ Sexual function for men and women is assessed by using the International Index of Erectile Function-5^[27]^ and Female Sexual Function Index,^[28]^ respectively. Urinary function is assessed by using the International Prostate Symptom Score^[29]^ for men and color ultrasonography of residual urine volume for all.

The secondary outcomes include incomplete CRM rate, 3-year local recurrence, 3-year disease-free survival, 3-year overall survival, and other surgical outcomes. Incomplete CRM is defined as tumor within 1 mm from closest mesorectal fascia, or within 1 mm from closest levator muscle, or invasion into or beyond the insphincteric plane. Local recurrence is defined as recurrent disease in the pelvis or at the incision. Disease-free survival is defined as the time of surgery to recurrence or end of follow-up. Overall survival is defined as the time of surgery to the date of death from any cause or the end of follow-up. Surgical outcomes include operation time, intraoperative blood loss, temporary stoma, intraoperative perforation, time to first flatus, time to liquid diet intake, postoperative hospitalization days, postoperative complications, incidence of urinary retention, and postoperative mortality in 30 days.

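### The 72 per group and 80% power rest on incomplete CRM, a secondary outcome, so the declared non-inferiority study of QoL and efficacy has no size basis for its primary scores

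*Protocol article*

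**What the plan says.** Three sections of the protocol article bear on this.

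- **Outcome measures (2.4).** The primary outcomes are questionnaire scores: "The primary outcomes of this trial are to be scores of European Organization for Research and Treatment of Cancer QoL questionnaire-core 30 (QLQ-C30"), followed by QLQ-CR29, the Wexner score, the prostate symptom score and IIEF-5 for men, and the FSFI for women. The abstract gives the same list. Then: "The secondary outcomes include incomplete CRM rate, 3-year local recurrence, 3-year disease-free survival, 3-year overall survival, and other surgical outcomes".
- **Sample size (2.5).** The section opens with "This is a non-inferiority verification study with QoL and efficacy as the main index". Its inputs are CRM rates only. For the control group: "In the pilot study, incomplete CRM rate was 6.1% (2 out of 33 patients) in the L-ELAPE group". For the experimental group: "we assume that the rate of incomplete CRM in the L-ISR group was 8.1" percent, taken from a meta-analysis. The two probabilities in the formula "are the rates of incomplete CRM of the experiment group and the control group, respectively". With alpha 0.025, beta 0.2 and equal groups, "the sample size required for each group is 72 cases", and 159 patients in total after a 20% dropout allowance.
- **Data collection, management, and statistical analyses (2.7).** Groups are compared by Student t test and chi-square test, with Kaplan–Meier estimates and Cox regression for survival. No comparison against a margin is described.

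The formula itself (Figure 2) is not shown. Its legend lists n, alpha, beta, k, p and the two CRM rates, and no margin.

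**The concern.** Hypothesis type, outcome ranking and size basis should describe one trial, and here they do not. A reader of 2.5 would take 80% power as the power for the main index, which includes QoL. In fact it was calculated for an outcome that 2.4 ranks below every QoL and function score.

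What is at stake is what the trial may conclude. A non-inferiority statement needs a margin set in advance and a size that can exclude it. For the primary scores the article links neither to the 72 per group, and the planned tests look for a difference. A non-significant t test on a QoL score would not establish non-inferiority. Three of the six primary instruments apply to one sex only, so the full group size is not available for them.

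**Working it through.** **1. The plan's own figure.** Inputs from 2.5: control rate 0.061, experimental rate 0.081, alpha 0.025 (taken as one-sided, since sidedness is not stated), beta 0.2, equal groups.

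The inputs alone do not give 72. As a plain test of 6.1% against 8.1% (pooled variance under the null):

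n = [1.96 × √(2 × 0.071 × 0.929) + 0.842 × √(0.061 × 0.939 + 0.081 × 0.919)]² / 0.02² = 2,588 per group.

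So 72 requires a margin. With the usual unpooled non-inferiority formula, the distance between margin and expected difference that 72 per group can support is

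√[(1.96 + 0.842)² × (0.061 × 0.939 + 0.081 × 0.919) / 72] = √(7.85 × 0.1317 / 72) = 0.12.

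The margin this implies depends on how the expected 2-point difference enters:

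| Treatment of the 2-point difference | Implied margin |
|---|---|
| L-ISR 2 points worse, as assumed | 0.12 + 0.02 = 14 points |
| Difference ignored | 12 points |
| Difference entered with the opposite sign | 0.12 − 0.02 = 10 points |

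A 10-point margin with L-ISR 2 points worse would need 7.85 × 0.1317 / 0.08² = 162 per group.

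**2. The ranking.** Section 2.4 puts incomplete CRM among the secondary outcomes. Section 2.5 uses it as the only input to the size of a study whose main index is QoL and efficacy. If CRM is the efficacy index, its rank in 2.4 disagrees with 2.5, and QoL still contributes nothing to the size. If it is not, neither part of the main index has an identified size basis.

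**3. What the size can show for the primary scores.** No SD is given, so the result is in SD units. At 80% power and one-sided 0.025, with no true difference, the smallest margin that can be excluded is (1.96 + 0.842) × √(2/n). The same expression gives the difference detectable at two-sided 0.05.

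| n per group | Basis | SD units |
|---|---|---|
| 72 | Stated requirement | 0.47 |
| 64 | 159 × 0.8 = 127.2, halved | 0.50 |
| 36 | Assumed: half of 72 are of one sex | 0.66 |
| 29 | Assumed: 40% of 72 are women | 0.74 |

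**4. Whether that is enough.** This cannot be decided from the article. As an assumed illustration on a 0–100 scale with SD 20, a 10-point margin needs 63 per group, an 8-point margin 99 and a 5-point margin 252. At 72 per group, power runs from 22% (margin 5, SD 25) to 98% (margin 10, SD 15).

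**The case against.** The strongest defence is that 2.5 names efficacy alongside QoL, so sizing on incomplete CRM sizes the study on one of its two declared indices. That is a fair reading, and it would be wrong to say that the section declares QoL alone as the main index. It does not remove the conflict over CRM's rank in 2.4, and it leaves QoL without a size basis.

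A second defence is that a condensed article may leave margins and SDs for each instrument to a full protocol or analysis plan. That stands, and their absence alone is not the point. The point rests on statements that the article does make and that disagree.

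Three stronger readings are tempting, and the documents do not support them:

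- **The trial is underpowered for QoL.** The illustration above includes adequate and inadequate cases. Without an SD or margin, only unstated power can be shown.
- **A non-significant QoL difference will be reported as non-inferiority.** No such rule is written. The Discussion asks which operation gives better QoL, so a hypothesis of difference for QoL is also plausible.
- **The CRM size rests on a 14-point margin.** That follows only from one formula and one direction of the 2-point difference. The formula image is not shown, so a margin inside it cannot be excluded.

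**Conclusion.** The point holds as an inconsistency between the declared hypothesis, the outcome ranking, the size basis and the planned tests. The stated alpha, 80% power and 72 per group belong to incomplete CRM and cannot be carried over to the primary scores. It needs correcting because it determines which conclusions the trial can draw.

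Its size: about 0.47 SD can be detected or excluded at 72 per group, 0.50 SD at 64, and about 0.66 to 0.74 SD on the sex-specific scales. These figures assume one-sided 0.025 (two-sided 0.05 for detection), 80% power, equal groups and an unadjusted comparison, plus no true difference where a margin is to be excluded. The sex splits are assumptions with no basis in the documents. Because patients choose their operation, equal groups are not assured, and imbalance would enlarge these figures. For CRM, the implied margin is roughly 10 to 14 points, and 14 with the usual formula and L-ISR 2 points worse.

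**What to change.** - In 2.5, state that the 72 per group and 80% power apply to incomplete CRM, give the margin used, and say that they do not apply to the primary scores. Align this with the ranking in 2.4.
- State the difference that the planned size can detect or exclude for the primary scores, using the SD figures above, with the sex-specific scales given separately and their assumed splits labelled.
- Limit any non-inferiority conclusion to an outcome with a prespecified margin, judged by a confidence interval against it. Report QoL as an estimated difference with a confidence interval unless a margin is set.

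This restatement costs a revised power and precision paragraph and a narrower claim, with no extra patients. Stating the CRM margin may expose a further question: a 10-point margin at the assumed rates would need 162 per group.

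The alternative is to make incomplete CRM primary or co-primary. That changes a primary outcome in a trial running since September 2018, so its cost is a formal, dated amendment rather than a wording change. It would still leave QoL in need of its own margin or an estimation-only aim.

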## Introduction

1

Colorectal cancer is the fourth most commonly diagnosed malignancy and the second predominant cause of cancer-related death worldwide.^[1]^ According to the data from the International Agency for Research on Cancer (IARC), rectal cancer would rank 8th in terms of incidence, accounting for approximately 40% of Colorectal cancer and constituting a severe global public health burden. Surgery is still the cornerstone of curative intent treatment for rectal cancer.^[2]^ Without regard to lower rectal cancer (LRC), it is undoubtful that anterior resection (AR) is the preferred surgical procedure for mid-upper rectal cancer.^[3]^ Abdominoperineal excision (APE) firstly reported by Ernest Miles in 1908 has long been considered the “gold standard” surgical management for LRC.^[4,5]^ Proven unappealing oncologic outcomes in APE compared to AR from several large-scale case series on resected rectal specimen, Holm et al presented a new approach of extended APE, also known as extralevator APE (ELAPE), without waist to reduce the risks of circumferential resection margin (CRM) involvement and intraoperative perforation for advanced tumors.^[6–8]^ Since Schiessel et al proposed their initial experience with intersphincteric resection (ISR) for LRC,^[9]^ a promising alternative to APE without permanent colostomy, the indication for ISR has been gradually assessed and strictly applied. Meanwhile, laparoscopic-assisted minimally invasive surgery is expected to allow meticulous precise operation with good visualization in narrow pelvic cavity.^[10]^

However, with the widespread adoption of neoadjuvant chemoradiation therapy (nCRT), management of LRC has shifted significantly.^[11,12]^ Yet, whether ultimate sphincter-preserving procedures, such as ISR, offer equal or better oncologic outcomes to LRC patients after favorable response from nCRT becomes controversial compared to APE or ELAPE.^[13,14]^ Surgery for LRC has to maintain a balance between radical tumor removal to minimize the risk of locoregional recurrence and patients’ desire, or postoperative quality of life (QoL).^[15,16]^ Postoperative continence is one of important outcome measures of QoL for LRC patients, and there are conflicting reports on the functional outcomes and QoL for patients after ISR compared to APE.^[16–19]^

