Thus, the aim of our trial is to prospectively compare QoL, perioperative complications and oncologic outcomes of laparoscopic intersphincteric resection (L-ISR) with laparoscopic extralevator abdominoperineal excision (L-ELAPE) in the patients with LRC after significant response to nCRT. The results are expected to provide new evidences for more detailed individualized therapies for LRC.

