## Discussion

3

Currently, the hot issue of the treatment for LRC located within 5 cm from anal verge is still being debated worldwide. The rapid improvement of surgical techniques and devices and universal utilization of preoperative treatment brings not only opportunities to management of LRC but new challenges to overcome. There is much controversy, however, on a new question as to which surgical option is more appropriate for patients with LRC after favorable response to nCRT to obtain better postoperative QoL and survival outcomes.

Although recent reports suggest that ultimate sphincter-preserving procedures, including ISR, may be feasible to cure LRC without compromise of resection margins and subsequent survival outcomes,^[13,33]^ advanced surgical technique is indispensable for ISR to deliver oncologic efficacy. There is a steep learning curve to successfully completing the L-ISR or L-ELAPE operation, including precise knowledge of rectal anatomy and its anomalies, to avert injury to critical adjacent structures. Perineal wound complications will be attached great importance on and biomaterial as a novel alternative will be used for pelvic floor reconstruction in the L-ELAPE group of our study. As for ISR, anastomotic leakage and anastomotic stricture must be taken into further consideration.^[34,35]^ Thus, prophylactic ileostomy will be performed for selected patients with higher risk of anastomotic leakage and digital rectal examination monthly after surgery is necessary in the L-ISR group.

Given the evident psychological and social impact of permanent colostomy required by APE surgeries, ISR was developed to provide a sphincter-preserving alternative.^[36,37]^ However, recent studies have challenged the assumption that global QoL is worse in patients with permanent stomas (eg, ELAPE patients).^[18]^ A matched-pair analysis comparing the long-term functional outcomes and QoL for 2 post-surgical populations indicated that ISR was associated with higher frequency of diarrhea and constipation than APE.^[16]^ Postoperative continence is exactly an important clinical outcome for LRC patient. Therefore, the pros and cons of each procedure will be discussed with patients and their families before decision making in our study. Psychological guidance, incontinence and stoma care education, and instruction of sphincter exercises will be added into the follow-up for both groups.

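### Section 2.5 puts QoL under a non-inferiority label that conflicts with the undirected QoL aim and the planned difference tests, and the sample size covers non-inferiority for incomplete CRM only

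*Protocol article*

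**What the plan says.** The hypothesis is stated once, at the opening of section 2.5 (Sample size): "This is a non-inferiority verification study with QoL and efficacy as the main index". QoL and efficacy share the one label.

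Section 2.4 (Outcome measures) makes QoL and function primary: "The primary outcomes of this trial are to be scores of European Organization for Research and Treatment of Cancer" questionnaires (QLQ-C30 and QLQ-CR29), together with four function instruments. The CRM outcome is placed lower: "The secondary outcomes include incomplete CRM rate".

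The Introduction ends with an aim to compare QoL, complications and oncologic results between the two operations, with no direction given. It also records that "there are conflicting reports on the functional outcomes and QoL for patients after ISR compared to APE". The Discussion describes the open issue as "which surgical option is more appropriate for patients with LRC after favorable response to nCRT to obtain better postoperative QoL and survival outcomes" and notes that "recent studies have challenged the assumption that global QoL is worse in patients with permanent stomas".

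The only numerical inputs in section 2.5 are CRM rates: for the control, "incomplete CRM rate was 6.1% (2 out of 33 patients) in the L-ELAPE group", and for L-ISR an assumed 8.1%. Section 2.7 plans Student t and chi-square tests of between-group differences.

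**The concern.** A non-inferiority hypothesis asks whether one operation is not worse than the other by more than a stated amount. A two-sided difference hypothesis asks whether the operations differ, and in which direction. Section 2.5 gives QoL the first kind. The aim, the background on conflicting QoL evidence and the planned tests all fit the second.

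The practical risk lies in how the result is reported. Read literally, a finding that QoL after L-ISR is not much worse would satisfy section 2.5 while leaving the QoL question unanswered. In the other direction, a non-significant t test could be presented as non-inferiority because of the label in 2.5, although that test does not assess non-inferiority.

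**Working it through.** **Step 1. Passages side by side.**

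| Place | What it implies for QoL |
|---|---|
| 2.5, opening sentence | Non-inferiority |
| Introduction, aim | Comparison, no direction |
| Introduction and Discussion, background | Direction of the QoL effect in dispute |
| Discussion, open issue | Which operation gives better QoL |
| 2.7, tests | Difference between groups |
| 2.5, calculation | QoL does not appear |

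As worded, 2.7 pairs the t test with categorical data and chi-square with continuous data. The pairing looks transposed, but both are difference tests, so the comparison above is unaffected.

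**Step 2. What the 72 per group addresses.** Inputs from 2.5: p_c = 0.061, p_e = 0.081, α = 0.025 (read as one-sided), β = 0.2, ratio 1. The formula image is not visible, and neither the text nor the figure legend gives a margin M, so 72 cannot be reproduced directly. It can be solved for M with the usual formula:

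n = (1.960 + 0.842)² × [p_c(1 − p_c) + p_e(1 − p_e)] / (M − 0.02)²

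The variance term is 0.0573 + 0.0744 = 0.1317, and 7.849 × 0.1317 = 1.034.

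- M = 0.14: 1.034 / 0.12² = 71.8, so 72 per group.
- M = 0.10: 1.034 / 0.08² = 161.5, so 162 per group. A 10-point margin gives 72 only if the 2-point difference enters with the opposite sign: 1.034 / 0.12².
- A test for a difference between 6.1% and 8.1% (two-sided 5%, 80% power) needs 2,588 per group.

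So 72 is consistent with a non-inferiority calculation on incomplete CRM and not with a difference test. No QoL mean, SD, margin or effect enters it.

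**Step 3. What the planned size gives for a two-sided QoL comparison.** The article gives no QoL SD or effect, so effects are in SD units and are assumptions. Two-sided α = 0.05, one scale, no multiplicity adjustment.

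Detectable difference at 80% power = (1.960 + 0.842) × √(2/n):

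- n = 72: 2.802 × 0.1667 = 0.47 SD.
- n = 63 (159 × 0.8 = 127.2, halved and rounded down): 2.802 × 0.1782 = 0.50 SD.

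If the SD on a 0–100 scale were 20 to 25 (assumed), 72 per group would detect 9.3 to 11.7 points.

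Power with 72 per group = Φ(d × √(72/2) − 1.96) = Φ(6d − 1.96):

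| True difference (SD) | Power |
|---|---|
| 0.5 | 85% |
| 0.4 | 67% |
| 0.3 | 44% |
| 0.2 | 22% |

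**The case against.** **The better-QoL wording is background.** It stands in the Discussion, describes a controversy in the field and covers survival as well. This is right. The point does not rest on it alone, because the formal aim is undirected and the tests in 2.7 look for a difference.

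**The analysis section already plans the right kind of test.** Largely so, and it makes the fix cheap. The conflict between 2.5 and 2.7 remains, and it concerns the primary outcome family.

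**A reader might infer that L-ISR can be declared a success with worse margins and no QoL gain.** The article does not support this, since it writes no success rule. The 8.1% against 6.1% is also a planning input and no evidence of harm: one rate is a meta-analysis average and the other is 2 of 33 pilot patients (exact 95% interval 0.7% to 20.2%).

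**A reader might infer that only a QoL gain could justify L-ISR.** That is a value judgement. The article presents L-ISR as a way to avoid a permanent colostomy, which could count as a benefit in itself. Non-inferiority on QoL could be a coherent design, but the article does not argue for it.

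**A reader might infer that the label prevents any finding on which operation is better.** It does not. The same confidence interval can show superiority, inferiority or non-inferiority. For the same reason, the chance of declaring non-inferiority when a true deficit lies inside some assumed margin would not show a defect, because that declaration would be correct.

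**Conclusion.** The point holds as an inconsistency in the stated hypothesis for the primary outcome family. Section 2.5 says non-inferiority for QoL, the aim and section 2.7 imply a difference, and the calculation in 2.5 covers incomplete CRM only. Because the hypothesis is stated in the article, this is more than a detail left to an unseen analysis plan.

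The consequence is a risk of misreporting: a result of not much worse, or a non-significant difference, could be taken to meet the declared aim. With the planned size, a two-sided QoL comparison has 80% power only for differences of about 0.47 SD (72 per group) to 0.50 SD (63 per group). These figures assume one scale, equal groups, two-sided 5% and a normal approximation. Groups are formed by patient choice, so a QoL difference would not by itself show an effect of the operation.

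The unstated CRM margin, the total of 159 and a secondary outcome driving the sample size are separate matters.

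**What to change.** Replace the opening of section 2.5 with wording to this effect:

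> The non-inferiority hypothesis applies to the incomplete-CRM outcome only. For QoL, the hypothesis is a two-sided between-group difference on [one named scale], reported with its 95% confidence interval. If the interval includes zero, we will report that no QoL difference was shown and will claim neither a QoL benefit nor non-inferiority on QoL.

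Add one sentence on precision: 72 per group gives 80% power for about 0.47 SD (about 0.50 SD with 63 per group), so smaller differences may go undetected.

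The cost is wording and the choice of one scale. It needs no extra patients or data and fits the difference tests in 2.7. The downside is the limited power. If the sponsor wanted 80% power for smaller effects, 0.4 SD would need 99 per group (198 / 0.8 = 248 in total) and 0.3 SD would need 175 per group (350 / 0.8 = 438), against 159 planned. The correction itself does not require that.

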**Methods::**

This prospective, single-center, non-randomized, controlled, non-blinded, phase I/II clinical trial is designed to enroll 159 eligible LRC patients who achieved favorable response to long-course nCRT (2 × 25 Gy). After informed consent, the patients will be assigned into the laparoscopic intersphincteric resection group or L-ELAPE group according to their own will. Standard radical laparoscopic surgeries will be performed for every participant. Then every participant will be followed up for 3 years. The primary outcomes are scores of QoL questionnaire-core 30, QoL questionnaire-colorectum 29, Wexner incontinence score, International Prostate Symptom Score (for male), International Index of Erectile Function-5 (for male) and Female Sexual Function Index (for female). The secondary outcomes consist of incomplete circumferential resection margin rate, 3-year local recurrence, 3-year disease-free survival, 3-year overall survival and other surgical outcomes.

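### The total of 159 does not follow from 72 per group with 20% dropout: it covers a loss of 9.4%, and the stated rate would need 180

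*Protocol article*

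**What the plan says.** Section 2.5 (Sample size) of the protocol article describes the trial thus: "This is a non-inferiority verification study with QoL and efficacy as the main index". The calculation itself is for the rate of incomplete CRM, with type I error 0.025, "type II error probability β = 0.2" and a ratio of group sizes of 1. Its result is that "the sample size required for each group is 72 cases". The section then goes from this result to the enrolment total: "we assume that there will be a 20% dropout rate. Therefore, at least 159 patients are needed in this specific trial".

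The Methods part of the abstract repeats the total as the planned enrolment: the trial "is designed to enroll 159 eligible LRC patients". No other dropout rate and no other total appear in the article.

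**The concern.** Section 2.5 prints a short chain: 72 per group, two equal groups, 20% dropout, therefore at least 159. Two groups of 72 make 144, so 159 adds only 15 patients, which looks too few to absorb a loss of one patient in five.

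The total is a headline design figure, given in both the abstract and the sample size section. If it does not provide for the loss the plan expects, the number left for analysis can fall below the number the plan calls required. How much this matters depends on the outcome. Incomplete CRM, the basis of the calculation, is a secondary outcome assessed around surgery. The primary outcomes in section 2.4 are QoL and functional scores, and section 2.3.2 schedules visits every 3 months for 3 years, so these are the outcomes exposed to follow-up dropout.

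**Working it through.** **Inputs, all from section 2.5:** 72 per group; ratio k = 1; dropout 20%; total 159; α = 0.025 (sidedness not stated, read here as one-sided because the design is non-inferiority); β = 0.2.

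**1. Attempt to reproduce 159.**

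- Required before dropout: 2 × 72 = 144.
- Standard allowance, N/(1 − d): 144/(1 − 0.20) = 180, or 90 per group.
- Shortcut, N × (1 + d): 144 × 1.20 = 172.8, so 173 (174 if each group is rounded up separately).

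The stated total is 180 − 159 = 21 patients short of the first and 173 − 159 = 14 short of the second. Rounding cannot explain either gap.

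**2. The loss that 159 covers.**

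1 − 144/159 = 15/159 = 9.4%, less than half of the stated 20%.

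**3. What remains from 159 at 20% loss.**

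- 159 × 0.80 = 127.2 in total, or 63.6 per group if the groups are equal.
- Shortfall against 144: 1 − 127.2/144 = 11.7%, about 12%.

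**4. Effect on CRM power, if dropouts are lost to that analysis.**

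The text gives no non-inferiority margin, and the formula figure is not available here, so 72 per group cannot be verified. Taking it as given that 72 provides 80% power, the standardised distance is 1.960 + 0.842 = 2.802. This scales with the square root of the group size, whatever the margin:

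- 2.802 × √(63.6/72) = 2.802 × 0.940 = 2.633
- Power = Φ(2.633 − 1.960) = Φ(0.673) ≈ 75% (74.6% at 63 per group, 75.2% at 64).

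**5. Effect on CRM power, if CRM is known for all operated patients.**

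If all 159 are operated on and assessed, 159/2 = 79.5 per group are available. This is above 72, so later dropout does not reduce CRM power.

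**6. Effect on the QoL outcomes.**

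The 72 was derived for CRM, so section 2.5 sets no target number for QoL. What can be given is precision. With equal groups and equal standard deviations, the half-width of a 95% interval for a difference in means is 1.96 × √(2/n) standard deviations:

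- n = 63.6: 1.96 × √(2/63.6) = 0.35 SD
- n = 72: 1.96 × √(2/72) = 0.33 SD.

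The interval is √(72/63.6) = 1.064 times as wide, about 6%. The scales given to one sex only rest on fewer patients still.

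**The case against.** The strongest objection concerns the consequence. Incomplete CRM is the only outcome with a stated power, and it is read from the resected specimen, so a patient who stops attending afterwards is not lost to it. On that view 159 leaves more than 72 per group for the powered comparison. This stands in part. A reader might infer from the arithmetic that the trial misses its 80% power, but the documents do not support that without a condition. Section 2.3.2 lists grounds for withdrawal without timing, so it is unknown how much of the 20% would occur before surgery or lead to exclusion from the CRM analysis. The objection does not repair the total, however. Section 2.5 itself applies the 20% to the CRM calculation and presents 159 as the result.

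A second objection is that the formula and margin are not visible. They are not needed: the fault comes after the formula, between three figures printed in the text. The missing margin does limit what can be said about power. Only the scaling in step 4 is available, and power at any particular margin would be an assumption.

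Third, a reader might infer that 10% was used by mistake, since 144 × 1.10 = 158.4 rounds up to 159. That is only one possible origin. Adding 20% to one group alone, 72 + 72 × 1.2 = 158.4, also rounds up to 159. The text describes neither, so the cause is unknown.

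Finally, a reader might object that 159, being odd, cannot give equal groups. This is immaterial: 159 is stated as a minimum, and patients choose their own operation (section 2.1), so no total guarantees equality.

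**Conclusion.** Wrong as written. With 144 required and 20% dropout, the total is 180 (173 by the weaker shortcut), not 159. The stated total covers a 9.4% loss. At the plan's own 20%, about 127 patients remain, 63–64 per group if evenly split, which is 12% below what section 2.5 requires. This rests only on figures printed in that section.

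The consequence is conditional. If dropouts are missing from the CRM analysis, power falls from 80% to about 75%, assuming that 72 per group is right and that the groups are of similar size. If CRM is known for every operated patient, later dropout costs no CRM power, and the loss falls on the QoL and functional scores, for which section 2.5 gives no required number.

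**What to change.** Make 72, 20% and the total agree in section 2.5, in one of two ways.

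- **Keep 159.** State that it covers about 9% loss for incomplete CRM, meaning patients without an evaluable specimen. Add that 20% follow-up dropout would leave about 63–64 per group for the QoL outcomes, and give the precision at that number. The article gives no support for a 9% rate over 3 years of follow-up, so this figure should be tied to CRM evaluability and not presented as the expected follow-up dropout. The cost is a sentence or two in section 2.5 and a less favourable statement about QoL; the abstract needs no change.
- **Keep 20% as the allowance for 72 evaluable per group.** State a total of 180 in section 2.5 and in the abstract. The cost is 21 more patients to recruit.

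The choice depends on which analysis the 20% was meant to protect, and section 2.5 should say so.
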